## Abstract

**Clinical trial registration:**

ClinicalTrials.gov, CTRI/2024/08/072027.

## Introduction

India has the highest burden of global suicide deaths (1) with a suicide rate of 12.69 in 2019 for both male and female (2). India’s proportion in the global suicide deaths increased from 27.3% in 1990 to 36.5% in 2019 among women and girls and from 16.7% in 1990 to 20.9% in 2019 among men and boys (1). According to WHO, the crude suicide rate in the age-group 15–29 years (per 100,000 population for both sexes) for India was recorded as 15.721 and is one of the leading causes of death among youth (1). Considering the current trends, it may be difficult for India to achieve the Sustainable Development Goal (SDG) 2030 target of reducing the age-standardized suicide death rate (ASDR; 12.1 per 100,000 in 2019) by a third (1).

The student population comprises 7.6% of deaths due to suicide (3). There has been a 25% increase in the socio-environmental and psychological risk factors among school and college students since COVID-19 pandemic, while there is a decrease in the protective factors (4). The alarming suicide rate among the students/youth (3) and the lack of accessible interventions and services in school and colleges provides the requisite thrust for evolving systems for mental health promotion in national educational settings.

Suicides and suicidal behavior are frequently the result of dynamic and complex interactions between various bio-psycho-social factors (5). Therefore, addressing these factors is vital for adapting and implementing any evidence-based models for suicide prevention.

The biological risk factors for suicides or suicidal behavior are mainly age (15–24 years age group has highest suicide rate in India), gender (female>male), biomarkers (e.g., dysfunctional brain circuitry, altered serotonin level), genetic factors, and presence of mental disorders/substance use (6). Importantly when such disorders oc-occur, the risk is magnified, with comorbidity serving as a critical determinant of suicidality (7). In contrast to the risk factors, several protective factors have been identified. These include problem-solving skills, coping skills, access to physical and mental health care, social connectedness, and healthy lifestyles are some of the protective factors (5).

The psychological risk factors are broadly organized into affective, cognitive, and social processes. Affective processes such as low self-esteem, worthlessness, neuroticism, hopelessness, difficulty in identification of emotions, ineffective emotional regulations, result into persistent and elevated risk of suicidal behavior in youth (6). Also, the cognitive processes such as impulsivity-aggression traits, selective-information processing are the predictors of suicidality among youths. The social processes such as loneliness (often mediated by other psychopathologies such as depression, anxiety) are associated with suicidality among youth (5).

In addition, recent advances in the literature suggest that psychiatric comorbidity further exacerbates suicide risk. Anxiety and depressive symptoms are significant predictors for the onset of suicidal ideaton and attempts among youth (7). Furthermore, individuals with multiple co-occurring mental health conditions exhibit substantially higher vulnerability to suicidal behaviors as compared to those with a single diagnosis (8). These findings underscore the compounded risks faced by individuals, particularly youth, who struggle with multiple mental health issues.

There is substantial evidence highlighting socio-environmental risk factors associated with youth suicide. These include child/adolescent maltreatment (any form of child abuse-physical, sexual or emotional), bullying (including cyberbullying) (9), peer and media influence, media reporting, drifting (getting disconnected from one’s support system-e.g. school, family), family constellation (disrupted family, parental loss may be due to death or divorce) (10), exam related factors (e.g., pressure to perform, failure, anxiety), minorities/ethnicity/caste-based discriminations, availability of lethal means, gender identity and sexual orientation, perceived stigma and availability of mental health resources (5).

Given the complex interplay of the risk and protective factors, suicide risk prevention requires multi-sectoral and multi-level approaches that consider evidence-based, universal, selective, and targeted strategies. Existing literature on suicide prevention, including studies conducted in educational settings, highlight a significant lack of implementation research in this field, particularly regarding the application of implementation frameworks in low and middle-income countries (LMICs). There is limited evidence supporting sucicide prevention programs in institutions of higher education and universities, underscoring the need to strengthen the evidence base in LMICs. A recent scoping review of 30 years of sucicide prevention in university students identified major gaps in efficacy, effectiveness and cost-effectiveness (11, 12). WHO also emphasizes that youth suicide prevention remains under-prioirtized in many LMICs, with limited integration into educational systems (13). This gap highlights the urgent need for contextually and culturally relevant implementation research within educational settings in LMICs like India.

The National Suicide Prevention Strategy (NSPS) of India aims at reducing suicide mortality by 10% by establishing effective surveillance mechanisms (by 2025) (14), integration of suicide prevention services via District Mental Health Programme in all districts (by 2027) (14), and integrating a mental wellbeing curriculum in all educational institutions (by 2030) (14). Additional objectives of the NSPS aim at strengthening leadership, fostering partnerships, and building institutional capacity at national level. The strategy also aims at capacity building at the level of health services for provision of suicide prevention services, promote community resilience and societal support, reducing stigma attached to suicidal behavior and advancing surveillance of suicide and evidence-based research (14).

The alarming suicide statistics among youth (3), an evidence-base on effectiveness of comprehensive multi-component intervention approaches including recommendations on implementation strategies under NSPS, highlight the urgent need for developing evidence-based suicide prevention model/s in educational campuses that are socio-culturally appropriate, acceptable, scalable and sustainable in resource-constrained settings.

In the present study interventions are specifically selected using the expert consensus method after considering their cost-effectiveness, universal approach, feasibility in non-health care settings (school-less stigmatizing approach), national suicide prevention strategies recommended by the Ministry of Health and Family Welfare, UMMEED guidelines of the Ministry of Education, and WHO Live Life Framework for Suicide Prevention. These intervention components will be linked to each other using the Sakashita model for suicide prevention (15) based on findings of formative phase of research.

### Aims and objectives

The study aims to co-develop an implementation model for educational institutions for reducing risk of suicide behavior (perceived stress and depressive symptoms) and enhance help-seeking behavior through formative research.

The primary objectives are to (a) develop an implementation model for educational institutions for reducing risks of suicide behavior (perceived stress, depressive symptoms) and enhance help seeeking behavior through formative research, (b) optimize the model through repetitive cycles of implementation, evaluation and refinement and (c) scale and evaluate the final implementation model.

## Methods and analysis

### Study design

The study will adopt a concurrent mixed methods design, incorporating both quantitative and qualitative aspects that would be captured simultaneously. A formative research phase will be initially conducted before taking on the main study and it will be guided by the Updated Consolidated Framework for Implementation Research (CFIR) (16). Additionally, the evaluation of the implementation process will be structured using the RE-AIM framework (17).

### Study setting

This study will be conducted in selected districts of eight states and union territories in India. The states and union territories are self-governing administrative divisions, and each of them has a state government. The administrative authority in these regions is shared among the state government and the central government. The study in each state and union territory shall be overseen by investigators belonging to a local institution. These states, union territories and institutions offering oversight include Andaman & Nicobar Islands (Andaman and Nicobar Islands Institute of Medical Sciences, Sri Vijaya Puram), Arunachal Pradesh (Rajiv Gandhi University, Papum Pare), Assam [All India Institute of Medical Sciences (AIIMS), Guwahati], Karnataka [National Institute of Mental Health and Neuro Sciences (NIMHANS), Bengaluru], Kerala (Government Medical College, Kollam), Maharashtra [Tata Institute of Social Sciences (TISS), Mumbai], New Delhi [Institute of Health Behaviour and Allied Sciences (IHBAS)], and Rajasthan [All India Institute of Medical Sciences (AIIMS), Jodhpur].

Within each state and union territory, one district has been selected for the study except for states of Arunachal Pradesh, Assam, Karnataka and Kerala. These include South Andaman (Andaman & Nicobar Islands); Dibang valley, Lower Dibang valley, Lohit, Papumpare, Itanagar capital complex, and Lower Subansiri (Arunachal Pradesh); Kamrup Urban/Rural (Assam); East Delhi (New Delhi); Bengaluru urban and rural (Karnataka); Thiruvananthapuram and Kollam (Kerala); Thane (Maharashtra) and Jodhpur (Rajasthan). These districts have been identified based on the reported suicide rate (3) and in consultation with respective state education and health departments. Intervention will be implemented at educational institutes in the selected districts. Educational institutes in all spheres including government aided, government-tribal aided and private funded shall be included in the study. The coordinating site would be the Indian Council for Medical Research (ICMR), Headquarters, New Delhi. The estimated time of completion of data collection will be December 2026, and the results are expected in March 2027.

### Study clusters

The educational institutes in selected districts will serve as the clusters for the study. The institutes with school and/or pre-university students (grades 9 to 12) or college students (graduate and postgraduate levels, including professional courses; excluding doctoral) will be eligible to participate.

### Study population

The target population will be school, pre-university and college students across educational institutes in selected districts across the eight states and union territories. The educational institutes exclusively catering to adolescents with special needs (e.g., intellectual and developmental disability or any other) will be excluded. However, such students if enrolled in the institutes selected in the study, they shall be able to access the interventions offered as part of the study.

### Inclusion criteria

The institutes with school and/or pre-university students (grades 9 to 12) and college students (graduate and postgraduate level including professional courses) willing to participate in the study and provide consent shall be eligible for inclusion in the study.

### Exclusion criteria

Students enrolled in doctoral programs and seeking education in distance or online mode and those pursuing certificate courses of less than 1 year duration will be excluded from this study. Additionally, individuals refusing to consent or not interested in participating in the study.

### Sample size and sampling across sites

Each of the eight states/union territories participating in this study will choose 1 or a maximum of 2 districts for implementation. (except in Arunachal Pradesh where more than 1 district will be included to complete the sample size). The choice of the district/s will be based on a host of factors like number and diverse types of educational institutes, feasibility issues, as per consultation with the government officials and any other relevant factors such as high suicide rates (wherever available).

### Sample size for individual level effectiveness

The sample size for youth beneficiaries is calculated to detect a 0.20 effect size{Anticipated per SD effect size(reduction in depression score) = 0.2 (Baseline mean = 8.5; Endline mean = 7.5, SD = 5.0; ES/SD = 1/5 = 0.2)} in mean on the PHQ-9 score in a group (90% power, 2-sided 5% significance level), assuming a correlation of 0.5 between T1 (Baseline) and T4 scores (3 measurements, 6, 12 and 18 months from baseline), and non-response rate of 10%, The required sample size will be 400 students per strata (i.e., 400 for schools, and 400 for UG/PG college) of selected educational institutes.

Average size of the class per stratum could be used to determine the number of classes to be randomly selected from each stratum (e.g., if the average class size for 9 th and 10 th grade is 40, then (400/40 = 10)10 classes would be required to get the sample of 400 in this stratum). The unit for sampling at the college could be batch/year of study and a similar approach could be used to determine the number of units to be followed up.

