### Status and timeline of the study

The study has been sanctioned for the duration of 3 years, from 01.03.2024 to 28.02.2027.

Recruitment and data collection

Recruitment initiation: participant recruitment is ongoing.Data collection completion: Data collection is anticipated to conclude by December 2026.Results availability: The final results will be available within three months after the completion of data collection at each site.

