### Phases of study implementation

The study shall be carried out in three phases including Preparatory Phase, Phase I and Phase II as depicted in Table 2. The spirit figure of the phases is provided in Figure 2.

**Table 2 tab2:** Logic model for comprehensive mental well-being package scale up.

Phase	Preparatory phase	Phase 1	Phase 2
Duration (Months)	6	12 months	12–18 months
Key activities	Map and engage all leaders and policy makers (State and district education and health system) to gather support for adoption and implementation of intervention package in educational institutes Conduct workshops in sub sample of selected clusters (4–5 schools) to understand the barriers and enablers influencing adoption and adherence of intervention package	Minimum of 3 to 4 iterative cycles for model optimization with each cycle spanning for 2–3 months in 4–5 clusters of schools. Evaluation of implementation outcomes (Feasibility, utility, costing, sustainability and scalability) at baseline and at end of 2–3 months of implementation for each cluster Identification of barriers to service users -students and service providers-gatekeepers/DMHP	Implementation of Mref model Assessing risks of suicide behavior (perceived stress, depressive symptoms, low help-seeking) at baseline and at atleast at 6, 12 and 18 months Evaluation of implementation outcomes (Feasibility, utility, costing, sustainability and scalability) at baseline and at least at 6, 12 and 18 months
Key outcome	M0 + Model Mapping of stakeholders and resources Onboarding of Clusters Adaptation of measurement tools Developing SOPs for leaders/gatekeepers/youth champions/district mental health professionals	Mref Model Fine tuning of SOPs for leaders/gatekeepers/youth champions/district mental health professionals	Implementation of Mref. model in reducing suicide risk behavior in educational institutes

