### Phase 2 [implementation and evaluation of the refined model (Mref)]

This phase aims to implement the model (Mref) across all educational institutions over a period of 12–18 months. This shall be aimed primarily in collaboration with the district education and health authorities with research investigators mainly providing advisory and supportive roles. Guidelines, protocols and training material will be adapted to identify and train an implementation team at each institute for rolling out of the Mref model (Figure 4).

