### Data collection

Data collection will be conducted in a retrospective manner to document the activities undertaken and their frequency across three phases: the pre-implementation phase (e.g., initial meetings, development of training manuals), the refinement phase (pilot testing and adaptation of the intervention), and the implementation and sustenance phase (trainings, meetings, and other activities carried out as per the refined model framework). The activities will be cost separately for each type of educational institution, considering the heterogeneity in functioning and resource use.

For each category of activity, the corresponding quantity of resources for which financial allocations were made will be assessed through stakeholder interviews with implementation teams and a review of relevant records. Resource prices will be obtained from records on actual financial allocations made, supplemented by information from personnel interviews, administrative documents or standard cost databases. For activities performed by the research team to support the implementation of the strategies, shadow pricing will be applied to document the full implementation costs to facilitate potential scale-up. In contrast, activities conducted exclusively for research and evaluation purposes will be excluded from the costing analysis. Likewise, the opportunity cost of undertaking implementation activities will not be considered.

In parallel, the evaluation will capture the impact of the suicide risk reduction strategy on healthcare-seeking behaviors, specifically by measuring the change in the number of students accessing health services following referral by educational institution staff at three time points: baseline (pre-intervention), midline (6 months), and endline (12 months). The incremental costs of outpatient consultations resulting from these referrals will also be incorporated into the final cost of the implementation package.

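### On the protocol's own phase lengths, the 18-month visit (T4) named in the sample size falls about two months after data collection is due to end

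*Protocol article*

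**What the plan says.** All references are to the protocol article.

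- **Sample size for individual level effectiveness:** 400 students per stratum, to detect a PHQ-9 change from 8.5 to 7.5 (SD 5.0, effect size 0.2) with 90% power, two-sided 5% and 10% non-response, "assuming a correlation of 0.5 between T1 (Baseline) and T4 scores (3 measurements, 6, 12 and 18 months from baseline".
- **Table 2 (Phases of study implementation):** the duration row reads "Duration (Months) 6 12 months 12–18 months" for the preparatory phase, Phase 1 and Phase 2. Its Phase 2 column requires "Assessing risks of suicide behavior (perceived stress, depressive symptoms, low help-seeking) at baseline and at atleast at 6, 12 and 18 months".
- **Table 3 (Assessment time-points):** T3 is 12 months and T4 is 18 months after T1, with PHQ-9 and PSS-10 at every visit.
- **Phase 2 section:** "This phase aims to implement the model (Mref) across all educational institutions over a period of 12–18 months".
- **Status and timeline of the study:** "The study has been sanctioned for the duration of 3 years, from 01.03.2024 to 28.02.2027", and "Data collection is anticipated to conclude by December 2026". Study setting agrees: "The estimated time of completion of data collection will be December 2026, and the results are expected in March 2027".
- **Data collection (cost analysis):** students who access services after referral are counted at "baseline (pre-intervention), midline (6 months), and endline (12 months".
- **Primary outcomes:** a fall in perceived stress and depressive symptoms is listed, without a time point.

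**The concern.** The sample size, Table 2 and Table 3 all carry follow-up to 18 months. The phase lengths and the end of data collection leave less than 18 months after Phase 2 opens. If both stand, T4 will be absent for students whose baseline is taken when Phase 2 starts or later. The students who do have a T4 would be those with early baselines, and a baseline taken during Phase 1 comes from the small set of clusters used to optimise the model, before Mref is settled.

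Depressive symptoms belong to a primary outcome, and the primary outcomes section fixes no time point. The sample-size section is therefore the nearest thing in the article to a defined endline, and it points to a visit that the calendar does not accommodate.

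**Working it through.** **1. The stated 400.** Inputs from the sample-size section: d = 1/5 = 0.2, rho = 0.5, z = 1.960 + 1.282 = 3.242, m = 3 follow-up measurements, 10% non-response.

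- One-group paired T1 to T4: SD of the difference = 5 × √(2(1 − 0.5)) = 5; n = (3.242 × 5 / 1)² = 263; 263/0.9 = 293. This does not give 400.
- Two-group comparison of the mean of m follow-up scores: n = 2z²[1 + (m − 1)rho] / (m d²). With m = 3, n = 351; 351/0.9 = 390, within 3% of 400.

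Of the variants tried, only the second uses every stated input and comes close. It is a two-group formula, while the text describes change within a group, so it is a likely route to 400 and not a confirmed one.

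**2. The calendar.** Inputs: start 1 March 2024; preparatory phase 6 months; Phase 1 12 months; end of data collection read as 31 December 2026; project end 28 February 2027.

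- Phase 2 baseline: 1 March 2024 + 6 + 12 months = 1 September 2025.
- T3 = 1 September 2026. T4 = 1 March 2027.
- Follow-up available: 1 September 2025 to 31 December 2026 = 16 months, against 18 needed.
- Latest baseline for T4 by 31 December 2026: about 30 June 2025. Latest baseline for T3: 31 December 2025.
- Total of the phases: 6 + 12 + 12 = 30 months to 6 + 12 + 18 = 36 months. The upper end fills the sanctioned 36 months exactly.
- A 12-month Phase 2 ends at T3 and contains no T4.

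**3. Sensitivity to the length of Phase 1.** Table 2 states 12 months, but 3 to 4 cycles of 2 to 3 months span 6 to 12 months.

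| Phase 1 (months) | Earliest Phase 2 T1 | T3 | T4 | T4 by 31 Dec 2026? |
|---|---|---|---|---|
| 6 | 1 Mar 2025 | 1 Mar 2026 | 1 Sep 2026 | yes |
| 9 | 1 Jun 2025 | 1 Jun 2026 | 1 Dec 2026 | yes |
| 10 | 1 Jul 2025 | 1 Jul 2026 | 1 Jan 2027 | no |
| 12 (as stated) | 1 Sep 2025 | 1 Sep 2026 | 1 Mar 2027 | no |

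T3 fits in every row.

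**4. What losing T4 costs in power.** Take 400 × 0.9 = 360 evaluable students, the same d and rho, and ignore clustering.

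- Two-group formula: power = Φ(d / √(2[1 + (m − 1)rho] / (m × 360)) − 1.960). With m = 3 it is 90.8%; with m = 2 it is 87.3%. The number needed with m = 2 is 395, or 395/0.9 = 439 with non-response.
- Paired T1 to T3: Φ(0.2 × √360 − 1.960) = 96.7%.

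**The case against.** The strongest reply is that no T1 date is given. Table 3 counts visits from T1, the assessment section ties T1 to training and not to a calendar date, and recruitment is described only as ongoing. 1 September 2025 follows only if the phases run one after another at full length. The article calls the end of data collection anticipated or estimated, and the bars of the Gantt chart, which might show overlaps, are not visible in the text at hand.

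This stands as far as it goes. A reader might infer that the T1 to T4 comparison cannot be made at all; the documents do not show that, because a Phase 1 of nine months or less would save T4. But Table 2 states 12 months and calls 3 to 4 cycles a minimum, and workshops to settle Mref follow the cycles. Table 2 also places the 18-month assessment in Phase 2, so earlier baselines from the optimisation clusters would not evaluate Mref.

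Other stronger readings lack support:

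- **The sanctioned end is breached.** T4 on 1 March 2027 misses 28 February 2027 by one day, and the phases sum to exactly 36 months. That is a schedule without slack. The firm conflict is with December 2026.
- **An 18-month effect will be divided into a 12-month cost.** The 12-month endline in the cost section covers referral counts and the outpatient costs that follow from them. Other implementation costs run across all phases, and no horizon is given for the PHQ-9 effect in the cost ratio. The 0, 6 and 12 month points under Quantitative analysis concern only the projection of help-seeking. Neither section makes 12 months the last visit.
- **Eighteen months compares different seasons of the school year.** The article gives no academic calendar.
- **Baselines must roll over about 64 institutes per site.** That number serves the precision of the adoption rate. The effectiveness sample is 400 students per stratum, about 10 classes in the article's own example.
- **Power collapses without T4.** The figures above show that it does not.

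**Conclusion.** The point holds as an internal contradiction of limited size. Under the stated phase lengths, the earliest T4 counted from a Phase 2 baseline falls two months after the stated end of data collection, and the Phase 2 section permits a duration that contains no T4. The conclusion assumes consecutive phases of the length given in Table 2, baselines at or after the start of Phase 2, and a cut-off at the end of December 2026.

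The loss of power is between negligible and about 3.5 percentage points, depending on the formula behind the 400. The substantive harm is to the definition of the endline: the visit named for sizing a primary outcome may be missing, or present only for an early and possibly unrepresentative subset. A 12-month comparison is feasible and should be named before endline data are seen.

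**What to change.** Reconcile Study setting, the individual-level sample size, Status and timeline, Table 2, the Phase 2 section and Table 3 as follows.

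1. Name T3 (12 months) as the primary effectiveness endline.
2. Restate the sample-size and power basis for T1 to T3 with two follow-up measurements, and say which formula is used. If it is the two-group formula above, 400 becomes 439, or 400 is kept with 87.3% power stated.
3. Require baselines for the effectiveness cohort by 31 December 2025 so that T3 fits the window. Where baselines have already been taken, check their dates against this limit.
4. Report T4 descriptively where it is reached, with the number and source of the students who contribute.
5. State the time horizon of the PHQ-9 effect in the cost ratio so that it matches the 12-month referral-cost count.

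Alternatively, keep T4 and move the end of data collection so that it fits. With a baseline on 1 September 2025 that means at least to 1 March 2027, one day past the current sanction, and later for later baselines.

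The first route costs changes of wording and a registry update. The 18-month effect is then no longer a primary claim.

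### The 400 students per stratum does not follow from its stated inputs, carries no allowance for sampling whole classes, and is not said to be per site or study-wide

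*Protocol article*

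**What the plan says.** The section on sample size for individual level effectiveness (protocol article) sets out these inputs:

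- Effect: "Baseline mean = 8.5; Endline mean = 7.5, SD = 5.0; ES/SD = 1/5 = 0.2".
- Contrast and error rates: a difference "in mean on the PHQ-9 score in a group (90% power, 2-sided 5% significance level").
- Within-student correlation: "assuming a correlation of 0.5 between T1 (Baseline) and T4 scores".
- Follow-up and loss: "3 measurements, 6, 12 and 18 months from baseline), and non-response rate of 10"%.

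The result is "The required sample size will be 400 students per strata (i.e., 400 for schools, and 400 for UG/PG college").

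The next paragraph turns this into a sampling scheme by example: "if the average class size for 9 th and 10 th grade is 40, then (400/40 = 10)10 classes would be required". For colleges, "The unit for sampling at the college could be batch/year of study", with no size given. No ICC or design effect is among the inputs.

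The section on sample size for clusters sets the number of institutes per site from the precision of an adoption rate, not from PHQ-9. The section on quantitative analysis plans mixed-effects models with random effects, but nothing from that plan enters the student calculation.

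**The concern.** There are three linked problems.

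1. The stated number cannot be reproduced from the inputs printed beside it, so a reader cannot tell what it is meant to cover.
2. The section powers the comparison as if students were independent, then recruits them as whole classes. Classmates share delivery by design: Table 1 asks for at least two youth champions per class and aims for one gatekeeper-teacher per section. Their changes in PHQ-9 may therefore be correlated, which reduces the information in 400 students.
3. The scope of 400 is not stated. With eight sites, it decides whether 800 or 6,400 students (two strata of 400, once or at each of eight sites) are followed. It also decides whether the clustering gap matters for the main estimate or only for single-site estimates.

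At stake is the 90% power claim for depressive symptoms, which are part of a primary outcome.

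**Working it through.** **Inputs from the article.** Difference 1, SD 5.0, r = 0.5, power 90%, two-sided 5%, non-response 10%, classes of 40.

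**Step 1: reproduce the stated figure.**
- SD of change = 5 × √(2 × (1 − 0.5)) = 5.0, so the standardised change is 1/5 = 0.2.
- n = (1.960 + 1.282)² / 0.2² = 262.7, so 263 pairs (265 with the exact paired t).
- With 10% loss: 262.7 / 0.9 = 291.9, about 292 (295 from the exact t).
- Stated: 400. Ratio 400 / 292 = 1.37.

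Other one-group versions, each divided by 0.9, also miss: 80% power gives 219, 95% power 362, a Bonferroni correction over three visits 376, and the mean of three follow-ups minus baseline 196. The figures close to 400 come from two-arm formulas: 390 per arm with loss for the mean of three correlated follow-ups, and 395 per arm before loss for ANCOVA with one follow-up. The article describes a single-group change with no second arm.

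**Step 2: power of 400 if students are independent.**
- Responders: 400 × 0.9 = 360.
- Power = Φ(0.2 × √360 − 1.96) = Φ(1.83) = 96.7%.

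**Step 3: how much clustering the excess can absorb.**
- Largest design effect that keeps 90% power: 360 / 262.7 = 1.37.
- With 36 responders per class: (1.37 − 1) / 35 = 0.0106. With 40 per class: (1.37 − 1) / 39 = 0.0095. So the ICC of the change score must be about 0.01 or less.

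**Step 4: power over an assumed ICC range.** The article gives no ICC, so this range is an assumption. It applies to the school example, 10 classes with 36 responders each. Design effect = 1 + 35 × ICC; effective n = 360 / design effect; power = Φ(0.2 × √(effective n) − 1.96).

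| ICC of change | Design effect | Effective n | Power (normal) | Power (t, 9 df) |
|---|---|---|---|---|
| 0.01 | 1.35 | 267 | 90% | 83% |
| 0.03 | 2.05 | 176 | 75.5% | 66% |
| 0.05 | 2.75 | 131 | 63% | 53% |

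The last column allows for the between-class variance being estimated from only 10 classes.

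**Step 5: if 400 is per site and eight sites are pooled.**
- Responders per stratum: 8 × 360 = 2,880, in about 80 classes.
- At ICC 0.10 the design effect is 1 + 35 × 0.10 = 4.5 and effective n is 2,880 / 4.5 = 640.
- Power = Φ(0.2 × √640 − 1.96) = Φ(3.10) = 99.9%. At smaller ICCs it is higher. This assumes a common change across sites and no clustering beyond the class.

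**Step 6: the same 400 spread over more classes.** With 40 classes of 10, there are 9 responders each.
- ICC 0.03: design effect 1 + 8 × 0.03 = 1.24, effective n 290, power 92.6%.
- ICC 0.05: design effect 1.40, effective n 257, power 89%.

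**The case against.** The strongest reply has four parts.

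- **The arithmetic gap is in the safe direction.** This stands. 400 exceeds what the listed inputs need, and the mismatch alone costs no power. A reader might infer from it that the sample is too small; it does not show that.
- **The context points towards 400 per site.** The number of institutes is set per site, and each site stratifies its own list into schools and colleges. On that reading the pooled analysis has ample power. This is plausible but not stated, and the 90% claim is attached to 400 per stratum.
- **The analysis plan has random effects.** A reader might infer that the trial's standard errors will be too small because clustering was ignored. The article does not support that: it states no planned standard error for PHQ-9, and it plans mixed models, though without naming the grouping level. The omission lies in the planning calculation.
- **Ten classes of 40 is an example, and no ICC is given.** Both are true. The power table therefore describes the school illustration over an assumed range. It does not say which ICC applies, and the ICC of a change score may differ from that of a single PHQ-9 score. Nothing can be computed for colleges without a batch size.

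This is not detail that an article may leave to a fuller document. The article prints the inputs, the result and a worked sampling example, and they do not fit together.

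**Conclusion.** The point holds in limited form and should be fixed. It is certain that the listed inputs give 263 pairs, about 292 recruited, rather than 400; that no clustering allowance is stated although whole classes are to be sampled; and that the scope of 400 is unclear.

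The loss of power is conditional. For a single sample of 400 drawn as in the school example, 90% power survives only up to a change-score ICC of about 0.01. If 400 is per site and the sites are pooled, the shortfall concerns site-level estimates only, for which the article makes no explicit power claim.

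A reader might conclude that the study as a whole is underpowered. The documents do not support this, because it needs both an ICC they do not give and the study-wide reading of 400.

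**What to change.** 1. Restate the calculation as 263 complete pairs, 292 with 10% loss, multiplied by a declared design effect. If another formula produced 400, name it and show that it fits a single-group comparison.
2. Say whether 400 is per stratum per site or per stratum in total.
3. Give the power of the planned class-based sample over an ICC range, for the single 400 and for the pooled sample. Include an assumed batch size for colleges.

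These three changes cost only wording. The article also plans to dichotomise clinical outcomes at the median, so the restated text should say that the calculation covers the mean change and not that binary analysis.

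Optional, where feasible: keep 400 but draw fewer students from more classes in institutes already enrolled. Forty classes of about 10 give 93% power at ICC 0.03 and 89% at 0.05. The cost is real: four times as many classrooms per stratum (and per site, if 400 is per site) at each assessment, with recruitment already under way.
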